## Abstract

**Background:**

Acupuncture is widely used for pain diseases while evidence of its efficacy for sciatica is insufficient. We aim to explore the feasibility and efficacy of acupuncture with different acupoint selecting strategies for sciatica induced by lumbar disc herniation.

**Methods:**

This is a multicenter, three-arm, patient-assessor-blinded randomized controlled pilot trial. Ninety patients will be assigned randomly into 3 groups including disease-affected meridians (DAM) group, non-affected meridians (NAM) group, and sham acupuncture (SA) group in a 1:1:1 ratio. The trial involves a 4-week treatment along with follow-up for 22 weeks. The primary outcome is the change of leg pain intensity measured by the visual analogue scale (VAS) from baseline to week 4 after randomization. Secondary outcomes include functional status, back pain intensity, and quality of life. Adverse events will also be recorded.

**Discussion:**

The results will inspire the optimal acupuncture strategy for sciatica and help establish a better design as well as power calculation for a full-scale study.

**Trial registration:**

ChiCTR2000030680 (Chinese Clinical Trial Registry, http://www.chictr.org.cn, registered on 9 March 2020).

**Supplementary Information:**

The online version contains supplementary material available at 10.1186/s13063-020-04961-4.

## Background

Sciatica is characterized by radiating leg pain along the course of the sciatic nerve sometimes accompanied by back pain and neurological deficits [1]. The prevalence ranges from 1.2 to 43% globally based on controversial definitions [2]. Lumbar disc herniation is the leading cause of 85% of patients with sciatica [3]. Sciatica affects daily life and productivity and consumes more health resources when compared to low back pain [4].

Conservative treatments are the first-line options for sciatica [5, 6]. Medicine and epidural steroid injection are commonly used although long-term benefits are uncertain and side effects (e.g., headache and dizziness) or complications (e.g., epidural hematoma) occur sometimes [7–9]. Most pain and related disabilities could resolve in weeks [5], but up to 30% of patients were reported with pain lasting for 1 year or longer [10]. Therefore, long-term effective and safe conservative treatments might be potential solutions.

Acupuncture has been widely used for pain diseases. Meta-analysis indicated that acupuncture had a persistent effect on 4 chronic pains which decreased only 15% after 1 year [11]. However, high-quality evidence remains scarce for acupuncture treating sciatica [12, 13]. Acupoints play a key role in treatment that different acupoint selecting strategies could generate discrepant effects [14, 15]. To optimize acupuncture strategy for sciatica, this pilot study will evaluate feasibility and efficacy of acupuncture with different acupoint selecting methods. The hypothesis is that acupuncture on disease-affected meridians might have better effects. Reliable data will be used to develop a better design including sample size calculation for a further randomized controlled trial (RCT).

## Methods/design

### Study design

The detailed study process is illustrated in Fig. 1. We design this multicenter, parallel-group, patient-assessor blinded RCT following the Consolidated Standards of Reporting Trials (CONSORT) and the Standards for Reporting Interventions in Clinical Trials of Acupuncture (STRICTA) guidelines [16, 17]. The trial will be conducted in outpatient departments of 6 hospitals in 4 cities in China, including the Department of acupuncture, Union Hospital, Union Hospital, Tongji Medical College, Huazhong University of Science and Technology; the Department of acupuncture, Affiliated Hospital of Nanjing University of Chinese Medicine; the Department of Rehabilitation, the Central Hospital of Wuhan, Tongji Medical College, Huazhong University of Science and Technology; the Department of acupuncture, Shenzhen Hospital, Beijing University of Chinese Medicine; the Department of pain medicine center and traditional Chinese medicine, Peking University Third Hospital; and the Department of acupuncture, Dongzhimen Hospital Affiliated to Beijing University of Chinese Medicine. The Research Ethics Committee of Beijing University of Chinese Medicine has approved the study protocol (version 2.0, 13 January 2020) with an approval number of 2020BZHYLL0105. It was registered at the Chinese Clinical Trial Registry (http://www.chictr.org.cn) on 9th March 2020 with the registration number of ChiCTR2000030680. The protocol is reported in accordance with the Standard Protocol Items (SPIRIT) (Additional file 1).

**Fig. 1 Fig1:**
[figure not shown]
Flowchart of the trial procedure. DAM, disease-affected meridians; NAM, non-affected meridians; SA, sham acupuncture

### Patients

There will be 6 centers conducting this study to ensure recruitments where many patients visit doctors for sciatica every day. Eligible patients will be recruited from outpatient clinics through advertisements on posters, newspapers, and WeChat. To promote recruitment as well as compliance, all treatment during the study will be offered freely.

#### Inclusion criteria

The study will include both male and female patients (1) aged between 18 and 70 years; (2) having symptoms of sciatica for 1 month or longer from the onset, diagnosed as unilateral radiating leg pain below the knee with positive straight-leg raise test or at least one neurological deficit symptoms as paraesthesia, muscle weakness, or reflex abnormalities. The imaging evidence of lumbar disc herniation is requested on either magnetic resonance imaging (MRI) or computed tomography (CT); (3) leg pain intensity for 40 mm or more measured by the visual analogue scale (VAS) [18].

#### Exclusion criteria

Patients will be excluded if they meet any of the following criteria: (1) patients who have or are suspected to have severe spinal diseases (e.g., cauda equina syndrome) or progressive neurological symptoms (e.g., progressive muscle weakness); (2) patients with sciatica caused by other conditions than lumbar disc herniation; (3) patients who have undergone surgery for lumbar disc herniation within the past 6 months; (4) patients who plan to have spinal surgery or other interventional therapies during the first 4 weeks of the trial; (5) patients continually taking antiepileptic medication, antidepressant medication, opioids or corticosteroids; (6) patients who have cardiovascular, liver, kidney, or hematopoietic system diseases, mental health disorders, or other severe coexisting diseases (e.g., cancer); (7) patients who are pregnant, breastfeeding, or planning to conceive during the trial; (8) patients who received acupuncture therapy within the past 6 months.

#### Dropout criteria

Patients will be removed if they are unwilling to continue participation. The reasons for dropouts will be recorded.

### Randomization

An independent statistician will generate the random sequence by the central block randomization method using IBM SPSS Statistics, version 21.0 (International Business Machines Corporation, China). Eligible patients will be assigned randomly into the disease-affected meridians (DAM) group, non-affected meridians (NAM) group, and sham acupuncture (SA) in a 1:1:1 ratio. An independent researcher in charge of informing assignment will implement the allocation schedule through a centralized telephone randomization procedure. To ensure the allocation concealment, acupuncturists will make a call to ask for the information of assignment before the first treatment. The independent researcher will send messages containing allocation details immediately. Before randomization, trial information will be provided to each eligible patient. Researchers (doctors) will get written informed consent from eligible patients who are willing to participate.

### Blinding

Patients, outcome assessors, and statistician will be blinded to the assignment. Differences between groups present mainly at point selections and acupuncture performance. Blunt-tipped needles for blinding will be similar to conventional needles. Adhesive foam pads will be put on treating points to cover the difference in acupuncture performance (Fig. 2).

**Fig. 2 Fig2:**
[figure not shown]
Schematic diagram of acupuncture and sham acupuncture

### Interventions

All patients will receive advice for managing sciatica in daily life such as remaining active, using a hard bed, or losing weight. Based on the assignment, they will receive 12 sessions of 30-min treatments over 4 weeks (ideally 3 times a week with an interval of 1 or 2 days). Acupoints are predefined based on experienced acupuncturists’ consensus and literature review [19]. Locations of acupoints are all according to the WHO Standard Acupuncture Locations shown in Tables 1 and 2 and Fig. 3 [20]. Patients could ask for Celebrex (Pfizer Pharmaceutical Co., Ltd) from researchers with guidance, and the use will be recorded in detail.

**Table 1 Tab1:** Location of acupoints in DAM group

Acupoints	Location
Dachangshu (BL25)	In the lumbar region, at the same level as the inferior border of the spinous process of the fourth lumbar vertebra (L4), 1.5 cun lateral to the posterior median line.
Guanyuanshu (BL26)	In the lumbar region, at the same level as the inferior border of the spinous process of the fifth lumbar vertebra (L5), 1.5 cun lateral to the posterior median line
Huantiao (GB30)	In the buttock region, at the junction of the lateral one third and medial two thirds of the line connecting the prominence of the greater trochanter with the sacral hiatus.
Fengshi (GB31)	On the lateral aspect of the thigh, in the depression posterior to the iliotibial band where the tip of the middle finger rests, when standing up with the arms hanging alongside the thigh.
Xiyangguan (GB33)	On the lateral aspect of the knee, in the depression between the biceps femoris tendon and the iliotibial band, posterior and proximal to the lateral epicondyle of the femur.
Yanglingquan (GB34)	On the fibular aspect of the leg, in the depression anterior and distal to the head of the fibula.
Xuanzhong (GB39)	On the fibular aspect of the leg, anterior to the fibula, 3 cun proximal to the prominence of the lateral malleolus.
Zhibian (BL54)	In the buttock region, at the same level as the fourth posterior sacral foramen, 3 cun lateral to the median sacral crest.
Chengfu (BL36)	In the buttock region, at the midpoint of the gluteal fold.
Weizhong (BL40)	On the posterior aspect of the knee, at the midpoint of the popliteal crease.
Chengshan (BL57)	On the posterior aspect of the leg, at the connecting point of the calcaneal tendon with the two muscle bellies of the gastrocnemius muscle.
Kunlun (BL60)	On the posterolateral aspect of the ankle, in the depression between the prominence of the lateral malleolus and the calcaneal tendon.

One “cun” is defined as the width of the interphalangeal joint of patient’s thumb

**Table 2 Tab2:** Location of acupoints in NAM group

Acupoints	Location
Yaoyan (EX-B7)	In the lumbar region, at the same level as the inferior border of the spinous process of the fourth lumbar vertebra (L4), 3.5 cun lateral to the posterior median line.
Pigen (EX-B4)	In the lumbar region, at the same level as the inferior border of the spinous process of the first lumbar vertebra (L1), 3.5 cun lateral to the posterior median line.
Yinbao (LR9)	On the medial aspect of the thigh, between the gracilis and the sartorius muscles, 4 cun proximal to the base of the patella.
Ququan (LR8)	On the medial aspect of the knee, in the depression medial to the tendons of the semitendinosus and the semimembranosus muscles, at the medial end of the popliteal crease.
Ligou (LR5)	On the anteromedial aspect of the leg, at the center of the medial border (surface) of the tibia, 5 cun proximal to the prominence of the medial malleolus.
Fuliu (KI7)	On the posteromedial aspect of the leg, anterior to the calcaneal tendon, 2 cun superior to the prominence of the medial malleolus.
Gongsun (SP4)	On the medial aspect of the foot, anteroinferior to the base of the first metatarsal bone, at the border between the red and white flesh.

One “cun” is defined as the width of the interphalangeal joint of patient’s thumb

**Fig. 3 Fig3:**
[figure not shown]
Locations of acupoints and non-acupoints. DAM, disease-affected meridians; NAM, non-affected meridians; SA, sham acupuncture

#### DAM group

Semi-standardized treatment will be provided with acupoints on affected meridians in this group. There will be four obligatory acupoints and five adjunct acupoints. Obligatory acupoints are bilateral Dachangshu (BL25) and Guanyuanshu (BL26). Depending on the distribution of the pain, sciatica localized at the side of the affected leg will be treated with adjunct acupoints on gallbladder meridian including Huangtiao (GB30), Fengshi (GB31), Xiyangguan (GB33), Yanglingquan (GB34), and Xuanzhong (GB39). Sciatica localized at the back of the affected leg will be treated with adjunct acupoints on bladder meridian including Zhibian (BL54), Chengfu (BL36), Weizhong (BL40), Chengshan (BL57), and Kunlun (BL60). For patients with pain in both side and back, adjunct acupoints will be selected from the ten adjunct acupoints above based on the personal experiences of acupuncturists.

After strict disinfection of the skin around acupoints and acupuncturists’ hands using 75% alcohol, adhesive foam pads (10-mm diameter and 5-mm height) will be placed on all acupoints with patients in a prone position. Disposable stainless steel acupuncture needles (0.30 × 75 mm, Suzhou Huatuo Medical Instrument Co, Ltd) will be inserted in BL25 and BL26 on the affected side deeply to 40–70 mm. After performing twirling, lifting, and thrusting manipulations for about 10 s, patients are expected to have “de qi” sensation (a complex feeling including soreness, numbness, heaviness, distention and dull pain, etc.) radiating down to the affected leg. Other acupoints will be treated with needles (0.30 mm × 40/50/75 mm) inserted to normal depths to reach “de qi” sensation locally. All needles will be retained for 30 min.

#### NAM group

Nine acupoints on non-affected meridians will be used as follows: bilateral Yaoyan (EX-B7) and Pigen (EX-B4) and unilateral Yinbao (LR9), Ququan (LR8), Ligou (LR5), Fuliu (KI7), and Gongsun (SP4) on the affected leg. All acupoints will be treated by needles (0.30 × 40/50 mm) inserted into the skin with manipulations later to reach the “de qi” sensation. Other treatment settings are the same as those for the DAM group.

#### SA group

We select nine non-acupoints in this group with locations shown in Table 3. They are localized in the middle of the gallbladder meridian and bladder meridian as one selecting method for non-acupoints [21]. Blunt-tipped needles (0.30 × 25 mm) will be inserted only into the pad with no penetration into the skin. No “de qi” sensation is required in this group and other settings will be the same.

**Table 3 Tab3:** Location of non-acupoints in SA group

Non-acupoints	Location
NA 1 (bilateral)	In the lumbar region, 2.5 cun beside Dachangshu (BL25), in the middle of gallbladder meridian and bladder meridian.
NA 2 (bilateral)	In the lumbar region, 2.5 cun beside Guanyuanshu (BL26), in the middle of gallbladder meridian and bladder meridian.
NA 3	In the middle of Zhibian (BL54) and Huantiao (GB30) acupoints on the affected leg.
NA 4	10 cun above the popliteal crease, in the middle of gallbladder meridian and bladder meridian on the affected leg.
NA 5	5 cun above the popliteal crease, in the middle of gallbladder meridian and bladder meridian on the affected leg.
NA 6	In the middle of Weizhong (BL40) and Yanglingquan (GB34) acupoints on the affected leg.
NA 7	In the middle of Chengshan (BL57) and Waiqiu (GB36) acupoints on the affected leg.

One “cun” is defined as the width of the interphalangeal joint of patient’s thumb

### Outcomes

The primary outcome is defined as the change of leg pain intensity on VAS from baseline to week 4 measuring pain over the prior 24 h. The VAS presents as a 0–100 mm ruler with 0 representing no pain and 100 representing unbearable pain. The specific score will be determined by the distance from 0 to the patient’s mark.

Secondary outcomes include VAS for leg pain and back pain at other time points, Oswestry Disability Index (ODI) [22], the Sciatica Frequency and Bothersomeness Index (SFBI) [23], 36-item Short Form Health Survey (SF-36) [24], straight leg raise test [25], painDETECT questionnaire [26], global perceived recovery on 7-point Likert self-rating scale [27], the Credibility/Expectancy Questionnaire [28], blinding assessment and medicine use. The ODI plays a role in giving a subjective percentage score of function level for patients with low back pain through examining perceived disability in 10 activities of daily living. The SFBI measures the frequency and symptom severity with scores ranging from 0 to 24 respectively. SF-36 is used to assess the quality of life on eight aspects including physical functioning, bodily pain, role limitations due to physical health problems, personal or emotional problems, emotional well-being, social functioning, energy/fatigue, general health perceptions, and a single item that indicates perceived change in health. PainDETECT questionnaire is used to discern the variation of neuropathic pain as one common method. A 7-point Likert self-rating scale is used to assess the recovery compared to the onset with options from “completely recovered” to “worse than ever.” The Credibility/Expectancy Questionnaire is capable to assess the credibility and expectancy of patients. Maintenance of blinding will be determined by asking patients to report the group which they believe they had been assigned to. Categories and frequency of medicines use during the trial will be recorded in detail. Detailed arrangements of every outcome are shown in Table 4.

**Table 4 Tab4:**
[figure not shown]
Schedule of recruitment, interventions, and assessments

*DAM* disease-affected meridians, *NAM* non-affected meridians, *SA* sham acupuncture, *w* week, *VAS* visual analogue scale, *ODI* Oswestry Disability Index, *SFBI* the Sciatica Frequency and Bothersomeness Index, *SF-36* 36-item Short Form Health Survey

Adverse events will be recorded, valued, and treated timely. Continuous investigation and reexaminations will be conducted until the end of the study. Independent clinical specialists who are blinded to the assignment will judge the severity and relationship between adverse events and acupuncture. Sever adverse events will be reported to the principal investigator and the data and safety monitor board (DSMB) within 24 h after occurrence to determine subsequent participation. The occurrence ratio of adverse events will be calculated at the end of the study.

### Data management

Data will be collected clearly and completely on case report forms (CRFs). All original data sources will be preserved including CRFs, informed consents, and inspection results. An independent data manager is in charge of the completed CRFs, he will be asked to input data doubly for proofreading. All data related to the trial will be saved for at least 5 years after publication. Readers will be permitted to access the original data by contacting the corresponding author. Information on patients will remain anonymous including name, age, and telephone number. An independent DSMB is established to ensure the integrity of the research data. The DSMB will review the progress and decide whether a premature closure is needed or not.

### Quality control

The study protocol has been reviewed and revised by experts of acupuncture, orthopedics, statistics, and methodology. All researchers who conduct the study will attend a series of training to promote the implementation. Data will be monitored on 3 levels by the head of sub-centers, researchers from the Beijing University of Chinese Medicine, and the DSMB pre-set for this study. The Research Ethics Committee of Beijing University of Chinese Medicine will audit the study on a regular basis independently.

### Sample size

As a pilot study, we determine to use a convenience sample instead of a sample size calculation. Ninety patients will be enrolled in this trial, 30 in each group. The data of this pilot trial will be applied to facilitate the calculation of the sample size for a further RCT.

### Statistical analysis

Continuous variables will be described by means and standard deviations or 95% confidence intervals when following a normal distribution. If not, the data will be shown by medians and interquartile ranges. Categorical variables will be described by frequencies and percentages.

All data will be analyzed following the intention-to-treat principle primarily. A per-protocol analysis will be used for primary outcome as sensitivity analysis covering patients who complete at least 10 treatment sessions without obvious violation. Analysis of variance (ANOVA), Kruskal-Wallis H test, or chi-square test will be used to compare the equilibrium between three groups at baseline. As for outcomes, one-way repeated measures ANOVA or Kruskal-Wallis H test will be applied for continuous variables and chi-square tests or Fisher’s exact test will be used for categorical variables as appropriate. Data analyses will be performed using IBM SPSS21.0 with the statistical significance of two-tailed *P* < 0.05 as exploratory.

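### The test of the primary outcome is left open between a repeated-measures ANOVA and Kruskal-Wallis, neither adjusts for baseline VAS, and the non-normal summary omits the SD the pilot needs

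*Protocol article*

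**What the plan says.** The Outcomes section defines one primary quantity: "The primary outcome is defined as the change of leg pain intensity on VAS from baseline to week 4 measuring pain over the prior 24" hours.

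The Statistical analysis section does not name a test for that quantity alone. It covers all continuous outcomes together: "one-way repeated measures ANOVA or Kruskal-Wallis H test will be applied for continuous variables", with the choice left to what is appropriate. No baseline covariate is named for either test. Baseline enters only through the change score or as one of the repeated measurements.

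Description has its own rule: "Continuous variables will be described by means and standard deviations or 95% confidence intervals when following a normal distribution". The next sentence gives the alternative: "If not, the data will be shown by medians and interquartile ranges". Results are to be judged "with the statistical significance of two-tailed *P* < 0.05 as exploratory".

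On size and purpose, the Sample size section says "we determine to use a convenience sample instead of a sample size calculation", then "Ninety patients will be enrolled in this trial, 30 in each group", and adds: "The data of this pilot trial will be applied to facilitate the calculation of the sample size for a further RCT". The Background states the same purpose.

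**The concern.** Three things are fixed badly.

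1. **Two tests, two targets.** ANOVA compares means in millimetres. Kruskal-Wallis compares rank distributions and gives no mean difference. With both open, the plan does not say in advance what effect the primary analysis measures, and the choice could be made with outcome data in view.

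2. **No baseline covariate in either branch.** Every patient has a baseline leg-pain VAS, since it is both an entry criterion and part of the primary outcome. Leaving it out of the model gives up precision at 30 patients per arm.

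3. **The summary does not match the purpose.** A sample size for a trial on mean VAS change normally rests on a mean difference and an SD. If the data are judged non-normal, the planned summary contains neither.

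At stake is the value of the pilot as a source of planning figures, more than the validity of its P values.

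**Working it through.** **The plan's own figure.** The sample is a convenience sample, so there is no power calculation to reproduce. The only arithmetic is 3 × 30 = 90, which agrees.

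**Inputs.** From the protocol article: three arms, 30 per arm, two-sided 0.05, outcome a change on a 0–100 mm scale. Assumed, because the article gives none of them: SD 20 mm at each time point, baseline-to-week-4 correlation r = 0.5, and one arm (DAM) better than the other two by 15 mm. The ANOVA branch is taken as a between-group comparison of the change score.

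**Step 1: value of baseline adjustment.**
- Means of 15, 0 and 0 have a grand mean of 5, so the between-arm sum of squares is 30 × (10² + 5² + 5²) = 4,500.
- Change-score variance: 20² × 2(1 − r) = 400 × 1.00 = 400. Noncentrality 4,500 / 400 = 11.25; with 2 and 87 df, power is 0.85.
- Residual variance with baseline as covariate: 20² × (1 − r²) = 400 × 0.75 = 300. Noncentrality 4,500 / 300 = 15; with 2 and 86 df, power is 0.94.
- The gain depends on r. Residual variance relative to a single measurement, adjusted against unadjusted change, is 0.91 v 1.40 at r = 0.3, 0.75 v 1.00 at r = 0.5, and 0.51 v 0.60 at r = 0.7.

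**Step 2: value of the choice between the two named tests.** Same shift and SD, by simulation:

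| Change scores | ANOVA | Kruskal-Wallis |
|---|---|---|
| Normal | 0.85 | 0.82–0.83 |
| Skewed (gamma) | 0.84–0.85 | 0.90–0.97 |

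The rank test costs about 2 points with normal data and gains power with skewed data. Almost all of the distance between Kruskal-Wallis on change (about 0.83) and the adjusted model (0.94) is therefore due to baseline adjustment.

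**Step 3: what a data-driven switch would do.** The article states no rule, so one was assumed: use Kruskal-Wallis if a Shapiro-Wilk test at 0.05 rejects in any arm. There were 4,000 simulated trials per scenario, with SDs of about 21–25 mm.
- Rank branch taken in about 15% of trials with exactly normal data, 13–16% with bounded near-normal data, and 98–99.8% with skewed or responder-mixture data.
- Type I error of the two-stage rule: 0.044 to 0.055.
- The two tests disagree on significance in 2–3% of null trials and in 4–18% of trials with an effect (a 12 mm shift, or 12 percentage points more responders).

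**Step 4: what the median/IQR summary does to the next sample size.** If a reader had only the IQR and took SD = IQR / 1.349, the sample size scales with SD²:
- Skewed data: (19.11 / 21.55)² = 0.79 times that from the SD itself.
- Responder mixture: (29.10 / 25.11)² = 1.34 times.

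For scale, a two-arm comparison with 80% power for a 15 mm difference needs 28, 44 or 63 per arm at SD 20, 25 or 30. If the SD is reported, its 95% interval runs from 0.80 to 1.34 times the estimate from one arm (29 df), or 0.87 to 1.17 times if pooled (87 df).

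**The case against.** The strongest reply has four parts.

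- **A reader might infer that normality decides the test.** The descriptive rule sits just above a parametric/rank pair, so the inference is natural. But the normality condition is written for description only; nothing attaches it to the test. What stands is that no trigger is written for the test at all.
- **A reader might infer that the rank branch loses the SD, or that only that branch lacks baseline adjustment.** Neither follows. The team holds the raw data, so an SD can be computed whichever test is run. In the normal branch, a confidence interval for a mean converts to an SD once n is known. The ANOVA branch names no covariate either.
- **A reader might infer that the switch costs much power or inflates error.** It does neither: about 2 points on normal data, a gain for the rank test under skew, and type I error near 5%.
- **This is an exploratory pilot, and a condensed article may leave model details to a fuller document.** The exploratory label does lower the inferential stakes. It does not touch the estimation purpose, which is the pilot's declared use. Silence on details would be no finding, but here the article does state the method, and states it as an either/or.

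**Conclusion.** The point holds in a limited form. The primary outcome has no single pre-specified test, the two candidates estimate different things, and neither uses baseline VAS as a covariate. The summary planned for non-normal data fits the sample-size purpose poorly because the SD is not among its planned outputs.

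The main measurable loss is the missing baseline adjustment: about 0.85 against 0.94 power under the assumed SD, correlation and effect, smaller if the correlation is higher and larger if it is lower. The factors of 0.79 to 1.34 in a future sample size apply only to someone who must work from the published IQR; the trial team need not. All these figures rest on assumed VAS distributions, since the article gives none.

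Given the convenience sample and the exploratory P values, this is a modest improvement to make, not a threat to the trial's validity.

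**What to change.** In the Statistical analysis section:

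- Name one primary analysis in advance: a linear (or mixed) model for week-4 leg-pain VAS with arm as the factor and baseline VAS as a covariate, reporting between-arm mean differences with 95% confidence intervals whatever a normality check shows.
- Keep Kruskal-Wallis, or another rank method, as a named sensitivity analysis. This is worth having because it can be the more powerful test under skew.
- Always report mean and SD by arm for the VAS outcomes, and add median and interquartile range if the data are skewed.

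The cost is a change of wording and slightly more analysis work. Patients, visits, data collection and sample size are unaffected. The one downside is that the headline estimate stays mean-based even if the data prove skewed; the rank sensitivity analysis and the added medians cover that.

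### The repeated measures ANOVA named for continuous outcomes drops patients with any missing visit in the model, which does not fit the stated intention-to-treat principle unless missing values are handled first

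*Protocol article*

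**What the plan says.** The Statistical analysis section of the protocol article sets the principle: "All data will be analyzed following the intention-to-treat principle primarily". For outcomes, "one-way repeated measures ANOVA or Kruskal-Wallis H test will be applied for continuous variables". The software is SPSS 21.0, and P values are two-sided and exploratory.

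One sensitivity analysis is named: "A per-protocol analysis will be used for primary outcome as sensitivity analysis covering patients who complete at least 10 treatment sessions without obvious violation". The Interventions section sets the full course at 12 sessions.

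The Outcomes section defines the primary outcome as change in leg pain VAS from baseline to week 4, and makes leg pain VAS at other time points secondary. The Abstract gives 22 weeks of follow-up. The visit schedule (Table 4) is not reproduced in the text available.

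Under Dropout criteria, "Patients will be removed if they are unwilling to continue participation", and then "The reasons for dropouts will be recorded".

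Under Sample size, "Ninety patients will be enrolled in this trial, 30 in each group". This is a convenience sample, and its data are meant to inform the sample size of a later trial.

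**The concern.** The principle and the named test pull apart. Intention-to-treat calls for all randomised patients to be analysed in their allocated groups. Classical repeated measures ANOVA needs a complete row for each patient: one missing visit among those in the model removes the patient and every value already observed, including week 4. Followed as written, with nothing done first about missing values, the method does not deliver the principle.

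The named sensitivity analysis does not help. Per-protocol restricts the set by sessions received and adherence, which are determined after randomisation. It asks about treatment received and leaves untested what is assumed about patients whose VAS is missing.

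Two things are at stake. With 30 patients per arm, discarding observed week-4 values costs precision. If those who miss visits differ from those who do not, the mean difference and SD passed to the next trial's sample size calculation carry that selection.

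**Working it through.** There is no power calculation or dropout allowance to reproduce. The only arithmetic in the plan, 3 × 30 = 90, agrees. What follows is illustrative.

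**Inputs**
- From the document: 30 patients per arm, 90 in all. Baseline leg pain VAS can be taken as observed for everyone, because the inclusion criteria require at least 40 mm.
- Assumed: missingness m per post-baseline visit of 3%, 5% or 8%, independent between visits; k = 3 to 6 post-baseline visits in the model.

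**Step 1: patients lost to listwise deletion, 1 − (1 − m)^k**

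| m | k = 3 | k = 4 | k = 5 | k = 6 |
|---|---|---|---|---|
| 3% | 8.7% | 11.5% | 14.1% | 16.7% |
| 5% | 14.3% | 18.5% | 22.6% | 26.5% |
| 8% | 22.1% | 28.4% | 34.1% | 39.4% |

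The range is about 9% to 39%. At m = 5% and k = 4, 90 × 0.95^4 = 73.3 patients remain, or 24.4 per arm.

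**Step 2: how much of that loss is avoidable at week 4.** Some lost patients have no week-4 value under any method. The share with an observed week-4 VAS that is nevertheless discarded is (1 − m) − (1 − m)^k.
- m = 3%, k = 3: 0.970 − 0.913 = 5.7%, about 5 of 90.
- m = 5%, k = 4: 0.950 − 0.815 = 13.5%, about 12 of 90.
- m = 8%, k = 6: 0.920 − 0.606 = 31.4%, about 28 of 90.

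**Step 3: precision of a two-arm week-4 contrast.** The 95% half-width in SD units is about 1.96 × √(2/n).
- All 30 per arm: 1.96 × √(2/30) = 0.506.
- m = 5%, all observed week-4 values (n = 30 × 0.95 = 28.5): 0.519.
- m = 5%, k = 4, listwise (n = 24.4): 0.561, which is 8% wider than 0.519.
- The ratio √[(1 − m)/(1 − m)^k] runs from 1.03 (m = 3%, k = 3) to 1.23 (m = 8%, k = 6).

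**Step 4: cases where the loss is smaller**
- Clustered missingness: if 10% of patients drop out and nobody else misses a visit, listwise deletion loses 10% (81 of 90 remain) whatever the number of visits.
- Only baseline and week 4 in the model (k = 1): the loss is m, and (1 − m) − (1 − m) = 0, so no observed week-4 value is discarded.
- No missing data, or imputation before the test: all 90 are analysed.

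**The case against.** The strongest reply is that nowhere does the article say its tests use complete cases, and it says outright that the analysis is by intention-to-treat. The same tests can be run on imputed data, and a condensed article commonly leaves the imputation rule to the full protocol or SAP, neither of which is shown. This stands: the missing rule is not a fault, and a reader who infers that randomised patients will definitely be left out goes beyond the text. What remains is a stated choice. The article names a test that needs complete rows beside a principle that does not allow them to be required.

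Second, the article does not say that later visits enter the primary test. A Kruskal-Wallis test on week-4 change, or a model with baseline and week 4 only, would lose only patients without a week-4 value. This also stands, and it is why the point is conditional. But a repeated measures model is named for continuous outcomes in general, leg pain VAS is measured at other time points, and nothing confines the model to two of them.

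Third, a reader might take the dropout rule as removing patients from the analysis. It does not say so. It is a withdrawal rule in the Patients section and is compatible with intention-to-treat if data already collected are kept.

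Fourth, a reader might infer that the per-protocol analysis repeats the selection in the main analysis. It need not. Per-protocol selects on sessions received, listwise deletion on visits attended; a patient with six sessions and every assessment is outside the first and inside the second. Per-protocol beside a primary intention-to-treat analysis is also conventional. The fair criticism is only that it does not examine missing data.

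Finally, higher dropout in the sham arm is sometimes expected, but nothing here documents it: patients are blinded and treatment is free. No direction of bias can be claimed.

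**Conclusion.** The point holds in a limited form. The plan states intention-to-treat and names a method that, run in its classical form without prior handling of missing values, drops incomplete patients and can discard observed week-4 data. The one named sensitivity analysis narrows the population and cannot show whether missing data matter.

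The size is not fixed by the document. Under assumed independent missingness of 3-8% per visit over 3-6 visits, about 9-39% of patients would be lost and the interval for a week-4 contrast would be about 3-23% wider than with all observed week-4 values. Independence makes this the high side: clustered missed visits give less. The conflict at week 4 also depends on visits other than baseline and week 4 being in the model.

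The documents do not support saying that the plan analyses completers only, that withdrawn patients are excluded from analysis, or that the treatment contrast is biased in a known direction. This is worth changing because the better method is at hand and the pilot's estimates feed a later trial. It does not invalidate an exploratory pilot.

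**What to change.** 1. Replace the repeated measures ANOVA with a likelihood-based mixed model for repeated measures, available as MIXED in SPSS. Include all randomised patients with any observed VAS, with group, visit and their interaction, and take the week-4 group contrast in change from baseline as the primary estimate.
2. State that data already collected from patients who withdraw are kept in the analysis.
3. Describe the per-protocol analysis as supplementary, not as a check on missing data.

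A missing-data sensitivity analysis, such as delta-adjusted multiple imputation, would be a reasonable but optional addition in a pilot of this size.

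**Cost.** A few sentences of analysis wording, slightly more analysis work and no extra patients. The mixed model rests on a missing-at-random assumption, which should be stated; a patient with no post-baseline VAS adds no direct information to the week-4 contrast.

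**Timing.** The Trial status section gives recruitment as complete on 27 September 2020 and the study as finishing by the end of March 2021. The analysis wording can be changed before the final analysis. A rewritten dropout rule could help only visits still due and would not recover week-4 assessments already missed, so the fix does not depend on it.
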